### Randomisation

Participants will be individually randomised in a 1:1 ratio to receive either the Engager intervention in addition to usual care, or usual care alone. Randomisation will be achieved by means of a web-based system created by Peninsula Clinical Trials Unit (PenCTU). Randomisation numbers will be computer generated and assigned in strict sequence. Randomisation will be stratified to ensure balance between the two treatment arms across the two investigator centres, with each centre having an independent sequence list for an equal number of participants. At the point of randomisation, participants will be assigned the next randomisation number in the sequence.

Confirmation that randomisation has been performed will be communicated in an unblinded fashion to the investigator site staff and to key members of the central research team, via emails automatically generated by the randomisation website. A researcher (usually the same researcher who conducted the baseline interview) will visit the participant in prison to deliver a letter informing the participant of the randomisation outcome. The researcher will go through the letter with the participant, ensuring that they understand their grouping and when they will be seen next and by whom (researcher or practitioner).

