### Intervention

The intervention is designed to engage with individuals with common mental health problems who are close to release, developing a pathway of care in preparation for release and resettlement in the community. The intervention will be delivered in prison between 4 and 16 weeks prerelease and for up to 20 weeks postrelease. Providing they are still willing to engage, all participants will receive the intervention for 8 weeks postrelease. However, for those who need further support, the intervention can continue for an additional 12 weeks, although at a lower intensity. This flexible approach to the length of the intervention followed on from our pilot work, which indicated that, while for many participants 2–3 months was sufficient, others required support from the practitioner for a longer period.

Engager is a manualised, person-centred intervention aiming to address mental health needs as well as to support wider issues such as accommodation, education, social relationships and money management. It was developed by bringing together evidence from a realist review,^42^ focus groups, case studies and a formative process evaluation. It will be delivered by experienced support workers and supervisor team leaders with experience of therapy. A mentalisation-informed approach underpins all elements of the intervention. Use of existing practitioner skills (eg, those used in coaching, solution-focused therapy, behavioural activation, cognitive–behavioural therapy) is also key to intervention delivery.

At prerelease stage, practitioner and participant will develop a shared understanding of the participant’s needs and goals, recognising the links between emotion, thinking, behaviour and social outcomes. A goal attainment plan will be developed and followed, including liaison with relevant agencies and the participant’s social networks. Engagement will be maintained throughout the prerelease period; when required, all-day support will be given on release day.

Following release, the practitioner will provide support for the participant to re-enter the community and engage with services. They will continue to work with the participant and any relevant organisations to help them achieve their goals, while encouraging the participant to take responsibility for self-care. The practitioner will also prepare the participant for the end of the intervention, while liaising with relevant community organisations regarding continuity of care.

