### Contamination

There is unlikely to be significant contamination between the intervention and control arms of the study, although it is theoretically possible for: trainers to train practitioners elsewhere, practitioners to pass on skills and working practices to those treating control individuals, intervention materials to influence practice for control individuals and offenders to influence each other. However, the risk of contamination is considered low primarily because there is no alternative funded pathway for delivery of the substantive components of the intervention for those in the control arm. Engager practitioners form a separate team in prison and while other practitioners are informed about the intervention, (1) they are not trained in the detail, (2) they tend not to have contact with our participants who are selected for the study using case finding and (3) they don’t have governance arrangements in place to follow individuals into the community. Cluster randomisation to prevent contamination would have been theoretically possible by randomising at a prison level, but practically not feasible because prisons are clustered together in localities, with one for new entrants, so each cluster would have several prisons. Additionally, the prison system can be subject to sudden and significant changes to prison procedures and entrants and it was estimated that a minimum of six clusters would be required in order to ensure balance, and this would have incurred prohibitive costs.

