### Sample size

The sample size is based on the ability to detect a difference on the primary outcome only and not on the inclusion of baseline measures as covariate. On the CORE-OM, 5.0 points is the accepted Reliable Change Index in service evaluations.^53 54^ In contrast, 2.5 points is held as the upper limit of what would be considered a change compatible with equivalence ([name], personal communication, 2015) in trials comparing two interventions. Other trials using the CORE-OM for mental health interventions versus treatment as usual or waiting list controls have achieved mean between group differences in change score of between 3.5 and 7.8.^55 56^ An SD of 5.6 was found in the pilot trial.^41^ However, larger clinical studies have reported larger SDs of approximately 7.5.^57^

Given the uncertainty, in both SD and the appropriate minimally clinically important difference (MCID) for the CORE-OM, we calculated sample sizes for different scenarios based on the range of values for these two parameters (see table 2). This is equivalent to aiming to be able to detect a minimum effect size of 0.26 (ie, small to medium).

**Table 2 T2:** Sample size (for each group) based on different values of SD and MCID for the Clinical Outcomes in Routine Evaluation-Outcome Measure

		SD		
		5.5	6.5	7.5
Change to be detected (MCID)	5.0	26	36	48
	4.5	32	44	59
	4.0	40	56	74
	3.5	52	73	97

At 90% power and two-sided alpha of 5%.

MCID, minimally clinically important difference.

Based on the conservative scenario of an MCID of at least 3.5 and a common SD of 7.5, we will require CORE-OM data on 97 participants in each group at 90% power and 5% alpha. Using an attrition rate of 30%, 140 participants are required per group. Follow-up rates of 63% and 55% were achieved in feasibility and pilot work.^41^ However, with learning from the pilot trial and assistance from the new Community Rehabilitation Companies (CRCs), which now supervise virtually all prison leavers for at least 1 year, an attrition rate of 30% or less is achievable.

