### Data management and statistical analysis plan

All data will be treated confidentially and stored securely and anonymously. CRFs will be checked and signed at the research sites by a member of the research team before being sent to the PenCTU for double-data entry on to a password-protected database. All forms and data will be tracked using a web-based trial management system. Double-entered data will be compared for discrepancies, and discrepant data will be verified using the original paper data sheets.

All quantitative data analyses will be conducted and reported in accordance with Consolidated Standards of Reporting Trials recommendations. We will closely monitor the process of data collection during the trial providing flow diagrams summarising, by group, the numbers approached, recruited, randomised, followed up/lost to follow-up and outcome completion.

Primary analyses will be conducted on an intention-to-treat basis (ie, according to randomised group) and compare primary and secondary outcomes at 6-month follow-up between randomised groups on those with complete data sets. Outcomes will be compared using linear-regression-based methods, adjusting for baseline outcome scores and stratification variables (eg, investigation centre). Where necessary, outcomes will be transformed to ensure good regression model fit. A secondary analysis will compare primary and secondary outcomes between groups at all follow-up time points using a repeated measures approach. Reasons for missing data (including loss to follow-up and participant drop-out) will be documented and the baseline characteristics of those with and without missing data compared. Using different assumptions for missing data, we will undertake sensitivity analyses using various imputation models, comparing between group results to the completers’ primary analysis. We shall also explore the possibility of conducting secondary per protocol between-group comparisons. If possible, this will be based on a predefined minimum level of intervention receivership and using complier average causal effect analysis methods. The analyst will be blinded to group allocation and the analysis will be undertaken using STATA V.14.2.

A detailed statistical analysis plan will be prepared before any data analysis is conducted. The statistical analysis plan will be agreed with the trial steering committee.

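### Neither the sample size nor the stated primary model allows for correlation between men who share an Engager practitioner, a correlation that can arise in the intervention arm only

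*Protocol article*

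**What the plan says.** All references are to the protocol article.

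- **Delivery.** The Abstract describes Engager as one-to-one support. The Intervention section says "It will be delivered by experienced support workers and supervisor team leaders with experience of therapy", and adds that the skills practitioners already have are key to delivery. The Contamination section says "Engager practitioners form a separate team in prison". The Control group section gives controls usual care only. No section states how many practitioners there are or how men are assigned to them.
- **Allocation.** "Participants will be individually randomised in a 1:1 ratio", stratified by centre (Randomisation).
- **Sample size.** The section takes a difference of 3.5 points and an SD of 7.5 and concludes: "we will require CORE-OM data on 97 participants in each group at 90% power and 5% alpha". Allowing for 30% attrition raises this to 140 randomised per group. The section gives no ICC or design effect, and it says that the calculation does not use the baseline covariate.
- **Primary analysis.** Data management and statistical analysis plan specifies linear-regression-based methods, "adjusting for baseline outcome scores and stratification variables (eg, investigation centre"). The analyst is to be blinded to allocation. A detailed analysis plan, not shown here, is to be written before any data analysis.
- **Clusters.** The Contamination section discusses clusters only as a randomisation option that was rejected. It does not discuss clustering by the person who delivers the intervention.

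**The concern.** Individual randomisation makes participants independent at entry, but treatment can introduce dependence afterwards. If some practitioners get better results than others, men on the same caseload have correlated outcomes. Controls have no Engager practitioner, so the design is partially nested: clustered in one arm, independent in the other. The protocol gives some reason to expect practitioner differences, because delivery draws on whatever skills each practitioner brings.

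Centre adjustment does not deal with this. Centre is a main effect common to both arms and cannot absorb variation between practitioners within the intervention arm. Baseline adjustment reduces residual variance but leaves the correlation between men on one caseload in place. With any positive practitioner ICC, a model that stops at the named covariates would give a standard error that is too small, an interval that is too narrow and a type I error above 5%.

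**Working it through.** **Reproducing the plan's figure.** Inputs from the Sample size section: difference 3.5, SD 7.5, two-sided alpha 5%, power 90%.

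n per group = 2 × (1.960 + 1.282)² × (7.5/3.5)² = 96.5, rounded up to 97. All 12 cells of Table 2 reproduce in the same way under independence. Attrition: 97/0.70 = 138.6, so 139, which the plan rounds to 140. In reverse, 140 × 0.70 = 98 analysed per group, with power Φ(0.467 × √49 − 1.96) = 90.4%. No clustering allowance is hidden in these figures.

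**Adding practitioner clustering in one arm.** Assumed, because the documents give none of them: number of practitioners k = 6 to 10 with equal caseloads, ICC 0.01 to 0.05, and baseline-outcome correlation r = 0 (as in the plan's calculation) or 0.5.

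- Caseload m = 98/k
- Design effect in the intervention arm DE = 1 + (m − 1) × ICC
- Variance ratio for the difference VR = (DE + 1)/2
- True SE divided by independence SE = √VR; understatement = 1 − 1/√VR
- Type I error of the unclustered test = 2 × [1 − Φ(1.96/√VR)]
- Power using the true SE = Φ(0.467 × √49 / √(VR × (1 − r²)) − 1.96)

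Example, k = 8 and ICC 0.05: m = 12.25, DE = 1 + 11.25 × 0.05 = 1.56, VR = 1.28, √VR = 1.132. Type I error = 2 × [1 − Φ(1.73)] = 8.3%. Power = Φ(3.267/1.132 − 1.96) = 82% at r = 0. At r = 0.5 it is Φ(3.267/(1.132 × 0.866) − 1.96) = 91.5%.

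| ICC | k | True SE / independence SE | SE understated by | Type I error | Power, r = 0 | Power, r = 0.5 |
|---|---|---|---|---|---|---|
| 0.01 | 6 | 1.038 | 4% | 5.9% | 88% | 95% |
| 0.01 | 10 | 1.022 | 2% | 5.5% | 89% | 96% |
| 0.02 | 6 | 1.074 | 7% | 6.8% | 86% | 94% |
| 0.02 | 10 | 1.043 | 4% | 6.0% | 88% | 95% |
| 0.05 | 6 | 1.176 | 15% | 9.6% | 79% | 89% |
| 0.05 | 10 | 1.105 | 9% | 7.6% | 84% | 93% |

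The type I column does not depend on r, because the baseline covariate scales the true and the independence SE alike when the ICC is taken as that of the adjusted outcome.

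With k widened to 4 to 12, type I error at ICC 0.05 runs from about 7% to 12%. At ICC 0.05, the r that brings power back to 90.4% is 0.61, 0.47 and 0.39 for k = 4, 8 and 12. These are normal approximations. They ignore the degrees of freedom lost when few practitioners are available to estimate the variance component.

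**The case against.** A reader might infer that the 90% power is overstated and the primary standard error wrong. The documents do not support either as a fact, for four reasons.

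- **Power.** The sample size deliberately leaves out the baseline covariate that the analysis will use. At r = 0.5 and ICC 0.05 the gain brings power to about 89-93% for 6 to 10 practitioners. The plan also uses an SD of 7.5 against 5.6 in the pilot. With k = 8, ICC 0.05 and r = 0, power would be about 91% at SD 6.5 and 97% at SD 5.6. This objection stands, so restating a single lower power would count only the unfavourable adjustment. It answers the power question only, because baseline adjustment leaves the relative understatement of the SE unchanged.
- **The analysis plan may deal with it.** The wording on regression methods is broad, and detail is deferred to a document not shown. A practitioner effect is not excluded. This stands in part: it is not a proven error in the final model. But the article does name the primary adjustment set, practitioner is not in it, and the sample size is already fixed without an allowance.
- **Team size and ICC.** No section says that the team is small; with two centres and three prisons (Setting) that is only an inference. At ICC 0.01 the effect is minor. Both points stand, which is why the size is given as a range.
- **One practitioner per man.** Support workers and team leaders both deliver the intervention, and no caseload rule is stated. Shared delivery, or men with little contact, would weaken the correlation. This stands as a limit on the size of the effect.

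**Conclusion.** The point holds as an unaddressed source of correlation. One-to-one delivery by a separate team in one arm is stated, the sample size assumes independence, and the named model has no term for practitioner. If the analysis followed that model as written, any positive practitioner ICC would make the standard error too small: by about 4-7% at ICC 0.02 and 9-15% at ICC 0.05, with the inflated type I error shown above. This rests on the assumed 6 to 10 practitioners, equal caseloads, one practitioner per man and 98 analysed intervention participants. The direction does not depend on the number of practitioners, provided they share out the men in caseloads of more than one, but the size does. The validity of the standard error matters more here than power, which may well be adequate.

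**What to change.** 1. Record each man's main practitioner when he is allocated to a caseload, so that intervention men with little or no contact are still classified.
2. Before any data analysis, prespecify a partially nested mixed model for the 6-month CORE-OM: the planned covariates, a random practitioner effect in the intervention arm only, arm-specific residual variances, and Satterthwaite or Kenward-Roger degrees of freedom. Make it the primary model, or at minimum a named sensitivity analysis.
3. Report the estimated practitioner ICC with its interval.
4. State the expected number of practitioners, describe the 90% power as making no allowance for practitioner clustering, and show power over a range of ICC and baseline correlation.

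The cost is analysis-plan wording and one recorded variable. The trial is still recruiting, and practitioner records are already a planned data source for the economic and process evaluations. There are three downsides. The interval will be slightly wider. With few practitioners the variance component will be imprecise, which is an argument for the sensitivity-analysis option. And a practitioner code that exists in one arm reveals allocation to an analyst who is meant to be blinded. The model code should therefore be fixed before unblinding, or this model run after the blinded primary analysis is complete.

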### Trial management and independent committees

Members of the research team directly involved with the day-to-day running of the trial will meet fortnightly to discuss trial progress, with additional email and telephone exchanges as required. A full trial management group including health economists, statisticians, process evaluation researchers and a sponsor representative will meet quarterly to review trial progress.

The Engager trial steering committee (Chair: [name] and three other independent members including a patient and public involvement representative) will meet 1–2 times per year to oversee the conduct of the trial, safety and ethics. The trial steering committee formally agreed that given the social/psychological nature of the intervention, only limited safety monitoring would be required, and therefore an independent data monitoring committee was not required.

### Ethics and dissemination

We have obtained National Offender Management Service (ref: 2015–283) approval and local Trust governance approvals for each site (Devon Partnership NHS Trust, Dorset Hospital University Foundation NHS Trust and Lancashire Care NHS Foundation Trust). The study has also been adopted by the National Institute for Health Research (NIHR) Clinical Research Network and the study sponsor is Devon Partnership NHS Trust.

The trial will be conducted in accordance with the ethical principles outlined in the Declaration of Helsinki and those consistent with GCP. The trial steering committee will ensure adherence to these guidelines. Any amendments to the protocol will be submitted for ethical approval as appropriate.

Findings will be published in peer-reviewed journals and presented at local, national and international conferences to publicise and explain the research to key audiences. A final report will be submitted to NIHR.
